**Exclusion Criteria**

1. Subjects on weight altering medications, such as orlistat.
2. Subjects with eating disorder
3. Subjects on medications other than insulin and or metformin that may affect blood glucose level.
4. Subjects with abnormal hepatic function tests.
5. Subjects with nephropathy, defined in this case as an overnight albumin excretion rate of >200 mcg/min using a first morning urine sample collection.
6. Subjects with recurrent diabetes ketoacidosis (more than 2 episodes in the past 12 months), or recurrent severe hypoglycemia (more than 2 episodes of hypoglycemia with altered level of consciousness, requiring assistance to treat in the past year).
7. Pregnant, breast-feeding or the intention of becoming pregnant or not using adequate contraceptive measures.
8. Known or suspected allergy to metformin.
9. The receipt of any investigational drug within 6 months prior to this trial.
10. Active malignant neoplasms.
11. No access to a computer.
12. Subjects currently taking metformin for clinical purposes are not eligible to be enrolled in this study.

***Withdrawal Criteria***

A subject must be withdrawn from the study if any of the following applies:

1. Pregnancy or intention of becoming pregnant
2. Allergic reaction to metformin
3. Subject decides to withdraw from the study*.*
4. Subject may also be withdrawn from the trial at the discretion of the Investigator if judged non-compliant with trial procedures or due to a safety concern.
5. increasing hypoglycemia

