**Visit Procedures (See Table 1)**

We will keep a subject screening log and a subject enrollment log.

In case of any premature discontinuation of the trial, we will make every effort to call in the subject for a last visit. We will specify primary reason (adverse event, non-compliance with protocol or other) for discontinuation in the CRF. If the subject is not able to attend, we will complete the End of Trial Form and fill in the Drug Accountability Form.

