**Subject Compliance**

We will assess subject compliance with the study in 3 ways: a), From information downloaded from the meter on every 3rd day, (b), Dossette, (c), Contact with parents. There will be 2 criteria for compliance: (i) at least 6 distinct data downloads from the meter every month; and, (ii) less than 25% residual pills in the dossette at each visit.

g. Is any aspect of this research study being conducted in the Medical School or a non-UMMMC facility? If yes, please explain.

No.

h. Will hospitalization be required as part of this research study?

| Yes |  | No | X |
| --- | --- | --- | --- |

If yes, how long will subjects be hospitalized?

i. Will there be any material inducements or recruitment incentives given to research staff or research subjects as part of this research study? (e.g., direct payments, free hospitalization, care)

| YesX |  | No |  |
| --- | --- | --- | --- |

If yes, explain how much, the pay schedule, or any partial payments that will be given.

Each participant will receive $120 for the entire study. This payment will be made at the rate of $20 per visit for the 6 visits. This money will be issued as a gift card to a bookstore at each of the 6 visits.

*The committee is exceedingly sensitive to the threat of coercion that can stem from excessive compensation for participation in research. The IRB recommends hourly payments of $20/hr for every hour (or fraction thereof) the subject is involved in the study. This should include time in the hospital or clinic that is solely for the study, travel time, and time spent recovering from a procedure or an anesthetic agent used for a procedure. Time that the subject is unable to perform his/her routine activities of daily living due to study related issues should be included in this time. (Time required to perform multiple minor tasks should be lumped together; that is, filling out a questionnaire that takes 15 minutes on four different days constitutes one hour of labor, not four hours.) If reimbursed, cost of transportation ($0.35/mile), parking and meals should be noted. A bonus of up to $50 may be given for completion of a long term study or for studies that involve low risk but uncomfortable procedures (such as endoscopy, multiple blood samples for pharmacokinetic studies, gynecological examinations, etc).*

1. **DISCLOSURE OF CONFLICT OF INTEREST**

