**Include the following information:**

a. Estimate likelihood of occurrence, severity, and duration. If generally accepted quantitative estimates are available based on previous data, these should be stated. Otherwise, qualitative estimates such as “rare”, “occasionally", or “frequently” may be used. *The committee needs scientific information about drug/device side effects so as to best judge the pros and cons of the study.* ***Do not simply cut and paste the consent form “Risk” section into this part of the protocol.***

Risks associated with study procedure:

Some children and adolescents may become embarrassed when given a physical examination or asked detailed questions about their diabetes. Some may be bothered by having blood drawn due to fear of needles or concern about pain. A numbing cream used to minimize pain can cause a slight swelling at the application site. There is a minor risk of infection at the site of the needle stick. In about 1 in 20 cases, a child may faint or become sick to the stomach at the sight of a needle or when blood is drawn. There may be some discomfort or bruising at the site of the needle stick. To alleviate the pain of needle stick, EMLA cream will be provided for subjects who wish to numb the site of blood draw before the needle stick.

Risks associated with medications:

1. Metformin: As a result of participating in this study, subjects randomized to the metformin arm will receive metformin 1000 mg once daily by mouth for 9 months. This dose is within the range of normal starting dose of metformin for pediatric patients with either diabetes or polycystic ovarian syndrome. Common side effects associated with metformin therapy include nausea, loss of appetite, diarrhea, gas, and a metallic taste. These usually subside with time and do not necessitate discontinuing the medication. Lactic acidosis is a rare but potentially serious side effect that is more likely to occur in individuals with heart, kidney, or liver failure. Lactic acidosis is very rare in children with diabetes.
2. Insulin: Hypoglycemia is a recognized risk of insulin therapy. However, all our participants would have been on insulin therapy for at least 6 months prior to being enrolled in our study. Thus, they have the knowledge and skills to recognize and manage hypoglycemia. We will also conduct a session on our titration regimen during the Run-in phase to familiarize participants with the protocol and possible side effects such as hypoglycemia.

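### The withdrawal criteria take randomised participants out of the study, not only off the capsules, so later HbA1c is lost for reasons that can depend on treatment and may bias the primary comparison

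*Protocol*

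**What the plan says.** Protocol section 4b, Withdrawal Criteria, opens with "A subject must be withdrawn from the study if any of the following applies". The list under that lead-in includes "Allergic reaction to metformin" and "increasing hypoglycemia", the latter without a definition. Item 4 is worded differently: "Subject may also be withdrawn from the trial at the discretion of the Investigator if judged non-compliant with trial procedures", or for a safety concern. So a *may* item sits under a *must* lead-in. The wording throughout is leaving the study or the trial. Stopping the capsules while staying in follow-up is not offered.

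Visit Procedures says that after premature discontinuation "we will make every effort to call in the subject for a last visit", and that the main reason will be recorded, naming adverse event and non-compliance as examples. It does not say what is measured at that visit, and it does not keep the participant on the month 3, 6 and 9 HbA1c schedule.

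Three other places bear on the point:

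- Subject Compliance sets two criteria: a minimum number of meter downloads a month, and "less than 25% residual pills in the dossette at each visit".
- Section 8a, risks associated with medications: "Common side effects associated with metformin therapy include nausea, loss of appetite, diarrhea, gas, and a metallic taste".
- Section 8b has the safety officer review unblinded data, including gastrointestinal effects by arm, and make recommendations on removing subjects.

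HbA1c is the primary outcome. H1A compares consecutive values between arms by repeated-measures ANOVA.

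**The concern.** Randomisation makes the arms comparable at month 0. They stay comparable at month 9 only if the outcome is measured in everyone, or if those not measured are missing for reasons unrelated to arm and outcome. Here the protocol itself creates missing outcomes, and the triggers occur after randomisation and can be related to treatment. What is then compared is the participants who remained, who may differ between arms in tolerance, adherence and glycaemia.

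This is a matter of data collection, so it cannot be left to a statistical analysis plan. An analysis plan can choose a model for missing values, but it cannot recover HbA1c that was never drawn. At stake is whether a between-arm difference in HbA1c can be read as an effect of assignment to metformin.

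**Working it through.** **Step 1. Do the rules end follow-up?** The Withdrawal Criteria speak of leaving the study or trial. Visit Procedures offers one attempted visit. If that visit followed the month-9 procedures, it would give an HbA1c at the time of exit, not at the later scheduled months. By contrast, Other steps to minimize harm (section 8b) stops metformin alone during certain illnesses and does not say that the participant leaves. Drug-only stopping is thus already known to the protocol but is not used in the Withdrawal Criteria.

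**Step 2. Can the reasons depend on arm?**

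| Reason | Status in the text | Link to arm |
|---|---|---|
| Metformin allergy | mandatory | a true reaction can occur only on metformin |
| Increasing hypoglycaemia | mandatory, undefined | possible, but section 8a does not expect metformin to cause it |
| Non-compliance | discretionary | gastrointestinal effects may lower pill counts |
| Safety concern | discretionary | the unblinded safety officer can recommend removal |

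**Step 3. Does the attrition allowance cover it?** Inputs from the sample size section: effect 1.5, SD 2, two-sided 5%, power 80%, 29 per arm, 25% allowance, 74 in total.

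- Two-sample formula: n = 2 × [2 × (1.96 + 0.84) / 1.5]² = 27.9, so 28 per arm. The stated 29 is reproduced to within one.
- 29 × 1.25 = 36.25, rounded up to 37 per arm, giving 74. Reproduced.
- With 25% lost, 74 × 0.75 = 55.5 remain, or 27.75 per arm. The standard error is 2 × √(2/27.75) = 0.537. Power is Φ(1.5/0.537 − 1.96) = 79.8%.

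The allowance therefore roughly holds power. It does nothing about who is lost.

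**Step 4. How large could the bias be?** The protocol gives no withdrawal rate by arm and no HbA1c gap, so every value here is assumed. Let d be the share withdrawn in an arm, and g the amount by which their month-9 HbA1c would have exceeded that of the retained. The full-arm mean is the retained mean plus d × g. The bias in metformin minus placebo among those retained is therefore −(d_M × g_M − d_P × g_P). A negative value favours metformin.

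Same g in both arms:

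| Withdrawn, metformin vs placebo | g = 0.5 | g = 1 | g = 2 |
|---|---|---|---|
| 15% vs 5% | −0.05 | −0.10 | −0.20 |
| 25% vs 10% | −0.075 | −0.15 | −0.30 |
| 35% vs 15% | −0.10 | −0.20 | −0.40 |
| 25% vs 25% | 0 | 0 | 0 |

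Equal 25% withdrawal, but for different reasons:

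| g_M | g_P | Bias |
|---|---|---|
| −1 | 0 | +0.25 |
| −1 | +1 | +0.50 |
| +1 | 0 | −0.25 |
| +1 | −1 | −0.50 |

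For scale, 0.05 to 0.40 is 3% to 27% of the planned 1.5, and 0.50 is 33%. The background reports a between-arm difference of 0.6 in one adolescent trial. In the other, the changes (9.6 to 8.7 against 9.5 to 9.2) also differ by 0.9 − 0.3 = 0.6.

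**The case against.** A reader might infer that the rules remove metformin patients selectively and so tilt the result towards metformin. The documents do not support that, for these reasons:

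- The criteria apply to both arms, and treating physicians and patients are blinded.
- Withdrawal for non-compliance is discretionary. Subject Compliance attaches no withdrawal consequence to its pill-count and download thresholds, so reading them as automatic triggers joins two sections that the protocol does not join.
- Section 8a adds that the gastrointestinal effects usually fade and need not lead to stopping the drug. The capsule dose is also stepped up after two weeks.
- The protocol does not expect metformin to cause hypoglycaemia. If it did, those withdrawn could well have lower HbA1c, and losing them would work against metformin.
- The three-month run-in assesses general compliance before randomisation.

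A reader might also infer that the analysis cannot use those withdrawn. That is not established. The protocol names repeated-measures ANOVA without saying that incomplete cases are dropped, plans a time-to-event analysis that can use participants up to censoring, and may leave missing data to an analysis plan not shown.

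All of this stands, and it rules out any claim about direction or size. It does not remove the core point. Blinding does not equalise tolerability, the run-in cannot test tolerance of capsules not yet given, the safety officer is not blinded, and no analysis recovers measurements not taken.

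**Conclusion.** The point holds as a risk, not as a demonstrated bias. Followed as written, the protocol loses later primary-outcome HbA1c for post-randomisation reasons that can depend on treatment. The resulting bias may be nil, if rates and reasons match between arms, or may go either way. The figures of 0.05 to 0.40 points for unequal withdrawal, and up to 0.50 in either direction for equal withdrawal with different reasons, rest wholly on assumed values and show scale only. With 74 participants and comparable trials showing differences of about 0.6, a bias in the upper part of that range would matter. The amendment is worth making because it is cheap, not because the trial is shown to be invalid. The mismatch between the mandatory lead-in and the discretionary item is a separate drafting inconsistency that needs reconciling.

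**What to change.** Amend the Withdrawal Criteria and Visit Procedures as follows:

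1. Separate stopping study capsules from leaving follow-up. Leave the clinical reasons for stopping capsules unchanged, but state that meeting one of them, or being judged non-compliant, ends study drug at most and does not end follow-up.
2. State that every randomised participant keeps the scheduled HbA1c visits at months 3, 6 and 9 unless consent or assent for follow-up is withdrawn. Where a participant asks to stop, record whether this means the capsules or the follow-up.
3. State that participants are compared in the arm to which they were assigned.
4. Reconcile the *must* lead-in with the *may* in item 4.

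No clinical threshold is proposed here, and insulin management after stopping capsules stays with the clinical team. The planned sample size does not change. The cost is a short amendment and a few visits, already in the schedule, for participants off study drug. The estimate becomes a treatment-policy effect, somewhat diluted by those who stopped.

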***Rationale for Trial Population***

Because of the rising incidence of childhood obesity, and the increasing prevalence of double diabetes in the population, participants aged between 10 and 18 years will provide the best age range to study the effects of treat-to-target regimen plus placebo or metformin on HbA1c and fasting plasma glucose in children, adolescents and young adults.

c. Discuss the number of experimental and control subjects, and explain the statistical basis for the numbers.

**Subjects:** Two hundred subjects will be screened for this study. Of these, 74 subjects will be randomized to either the placebo or metformin arm of the study.

**Sample size calculation and Statistical Analysis:**

All patients will undergo a 3-month run in phase, during which they will be on detemir and aspart only, with no added metformin or placebo. (Please see a detailed explanation of the run-in phase under Trial Design above). At the end of the run-in period,patients will be assigned to one of the two treatment groups (placebo or metformin) using a random number generation process. Placebo and metformin will be offered in similar form, to ensure participants are blinded to their assignment. Group assignment will be established by a research pharmacist with no direct participation in the study; and principal investigator will not be informed of what group each individual is assigned to.

The primary outcome chosen to measure the impact of metformin on the management of “double diabetes” children is their level of glycosylated hemoglobin (Hb A1c, measured as a %). The secondary outcomes are: a) blood pressure (mmHg), b) waist circumference (cm), c) body mass index (BMI, kg/m2), d) lipid profile (LDL and HDL cholesterol and triglycerides (mg/dL)), e) ), leptin (ng/dL), and f) 25-hydroxyvitamin D (ng/mL), g) adiponectin (µg/mL ), and total daily dose of insulin.

All outcomes will be measured on an ongoing basis, at the beginning of the trial, and then at 3 months intervals during the entire study period. The intervention arm of the study will last 9 months. **Sample size calculations** are based on the simple comparison of paired means. Using a confidence level of 95% (Z (1-α/2) = 1.96 for a two-tailed test) and a statistical power of 80% (Z (1-β) = 0.84), calculated group sizes are 29 individuals for each arm of the trial. This number is based on the assumptions that 1) supplementing the treat-to-target protocol with metformin will decrease the Hb A1c level by at least 1.5 percent units, and 2) the standard deviation for Hb A1c levels in obese adolescents is estimated to be 2. Because of the duration of the study, and the possibility of loss to follow-up, a 25% attrition allowance has been made on the ‘n’ of 58, bringing the total number of participants to 74. This is a conservative approach to the sample size calculation, because the repeated measurements will, by construction, improve the power of the study, improving its ability to capture outcomes with more variability than expected.

**Subject Replacement:** To ensure adequate sample size to reach significance according to our power calculations, we will oversample by 25% for each arm of the study. This will enable adequate numbers despite predicted study attrition.

**Statistical analyses** will be conducted so as to capture both the absolute changes in serum values for the proposed outcomes, as well as “time-to-event” information allowing us to compare the 2 groups with maximum efficiency.

1) **H1A**: Metformin supplementation of treat-to-target insulin regimen of diabetes care will have an influence on levels of HbA1c over time.

Mean levels of HbA1c will be computed at each time point, applying arcsine transformation to approximate Normality. 95% Confidence Intervals (95% CI) will be constructed around these estimates. All results will be graphed for visual appreciation of possible trends. Consecutive HbA1c levels for patients with and without metformin will be compared using repeated-measures Analysis of variance (ANOVA). Analyses of Covariance will be modeled to account for possible confounding due to gender and age. Similar analyses will be applied to the FPG levels, using the logarithmic transformation instead.

2) **H1B**: Patients randomized to adjunctive metformin therapy will achieve a greater reduction in HbA1c and fasting plasma glucose than those on placebo.

Adjunctive metformin and placebo groups will also be compared using both a logistic model and an actuarial survival model for “time-to-event”, where the event of interest is the decrease of the HbA1c level to 8% or less, as the biological cutoff below which serum glucose levels are considered stabilized. Similar analyses will be applied to FPG levels.

3) **H1C**: Metformin supplementation of treat-to-target regimen of diabetes care will have a measurable influence on blood pressure, waist circumference, body mass index, lipid profile, leptin, adiponectin, and 25-hydroxyvitamin D.

Mean values for each one of these outcomes will be computed at each time point, applying appropriate transformations where needed to approximate Normality. 95% CIs will be constructed around these estimates. All results will be graphed for visual appreciation of possible trends. Consecutive measurements for patients with and without metformin will be compared using repeated-measures Analysis of variance (ANOVA). Analyses of Covariance will be modeled to account for possible confounding due to gender and age. Non-parametric equivalent of statistical tests will be used where necessary.

4) **H1D**: Transition from standard insulin treatment to treat-to-target regimen will provide better diabetes care for all patients. (Please see Table 2 below for a detailed explanation of the protocol for patient-directed forced-titration regimen).

Mean A1c levels at the beginning (-3mo) and at the end (0 mo) of the run-in period in all patients will be compared to subsequent mean A1c levels in the placebo group, using repeated measures ANOVA. Necessary adjustments for possible confounders will be carried out as described above.

d. Does the study involve randomization?

| YesX |  | No |  |
| --- | --- | --- | --- |

**If yes**, please describe process.

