There are only 2 randomized, placebo-controlled trials of adjunctive metformin therapy in adolescents with type 1 diabetes. In a randomized placebo controlled trial in children with type 1 diabetes who were treated for 3 months with adjunctive metformin, Sarnblad et al[43] reported a significant decrease in A1c from 9.6% to 8.7%(p<0.05) in the metformin group, compared to 9.5 to 9.2% (p=NS) in the placebo group. In another study, Hamilton et al[41] reported an HbA1c 0.6% lower in the metformin group than in the placebo group (P<0.035), after 3 months of therapy. Mean HbA1c at the end of the study was decreased by 0.3% in the metformin group, while it increased by 0.3% in the placebo group (p=0.03). Both studies reported no difference in mean body mass index and serum lipids in the metformin versus placebo group after 3 months of therapy. Hamilton et al[41] reported no significant changes in mean insulin sensitivity, measured by frequently sampled glucose after intravenous glucose tolerance test, after 3 months of metformin therapy in the metformin versus placebo group. Sarnblad et al[43], using hyperinsulinemic euglycemic clamp study, demonstrated no significant change in insulin sensitivity after 3 months between the groups, but they did report an increase in insulin sensitivity in the metformin group during the study (P<0.05). Hamilton et al[41] reported a significant change in the mean daily insulin dose in the metformin group in comparison to the placebo group after 3 months of metformin therapy of -0.14 vs. 0.02, P=0.01. However, Sarnblad[43] did not find a significant difference in the daily insulin dosage between the metformin and placebo groups after 3 months of therapy (1.1 vs. 1.3).

C. Gaps in current knowledge

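### The sample size of 29 per arm is right for two independent arms but is labelled a paired comparison, 74 does not fully cover 25% attrition, and the 1.5-point effect is unsourced and 2.5 times what the cited trials found

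*Protocol*

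**What the plan says.** Item 4c of the protocol, under *Sample size calculation and Statistical Analysis*, states that the calculations "are based on the simple comparison of paired means". The error rates are given as "Using a confidence level of 95% (Z (1-α/2) = 1.96 for a two-tailed test") and "a statistical power of 80% (Z (1-β) = 0.84"). Two assumptions follow: metformin lowers HbA1c by at least 1.5 percentage points, and the SD of HbA1c levels in obese adolescents is 2. From these, "calculated group sizes are 29 individuals for each arm of the trial".

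A 25% allowance for attrition is then put on the 58, "bringing the total number of participants to 74. This is a conservative approach to the sample size calculation". The reason given for that description is that the repeated measurements will add power. The *Subject Replacement* paragraph says "we will oversample by 25% for each arm of the study" and that this will leave adequate numbers despite the predicted losses.

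No source is given for the 1.5. In the background section on *Clinical Trials and Therapeutic Interventions*, the protocol describes the only two randomised placebo-controlled trials of adjunctive metformin in adolescents with type 1 diabetes. One "reported an HbA1c 0.6% lower in the metformin group than in the placebo group". The other found a "significant decrease in A1c from 9.6% to 8.7%(p<0.05) in the metformin group, compared to 9.5 to 9.2" per cent in the placebo group.

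**The concern.** Three statements in one short paragraph do not fit the design or the protocol's own evidence.

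- **Method.** Participants are randomised 1:1 to two separate arms, so the primary contrast is between independent groups. A paired comparison is a different calculation. It needs an SD of within-pair differences, or a correlation, and the protocol gives neither.
- **Attrition.** Adding 25% to the required number does not protect against losing 25% of those enrolled.
- **Effect size.** The whole calculation rests on a difference well above anything the protocol reports for this comparison. If the true effect is near the cited one, the trial has a low chance of detecting it, and nothing in the sample size paragraph tells the reader so.

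At stake is how the result will be read. The background section faults earlier trials for their small size. The protocol also asks whether titrated insulin alone might do as well as insulin plus metformin. A reader needs to know which differences this trial can and cannot detect.

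**Working it through.** **Inputs.** From item 4c: z = 1.96 and 0.84, difference 1.5, SD 2 (of HbA1c levels), 29 per arm, 25% allowance, total 74. Allocation is 1:1 (*Randomization*). From the background section: HbA1c differences in the two cited trials.

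**1. Reproducing 29.** Two independent means, normal approximation:

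n per arm = 2 × (1.96 + 0.84)² × (2/1.5)² = 2 × 7.84 × 1.778 = 27.9, so 28.

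With the noncentral t distribution, power is 78.7% at 28 per arm and 80.1% at 29. The t-test therefore gives exactly 29, and the stated number is the two-sample result.

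**2. Reproducing 74.** 29 × 1.25 = 36.25, rounded up to 37 per arm; 2 × 37 = 74. This matches the description of oversampling each arm by 25%.

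**3. What 74 covers.**

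- Completers after 25% loss: 74 × 0.75 = 55.5, against 58 required.
- Number needed to keep 58: 29/0.75 = 38.7, so 39 per arm and 78 in total.
- Attrition that 74 does cover: 1 − 58/74 = 21.6%.
- Power for 1.5 points at 55.5 completers (27.75 per arm): 78.3% by t-test. With the protocol's z constants it is 79.8%.

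**4. The effect in the cited trials.** The first reports a difference of 0.6. In the second, the changes are 9.6 − 8.7 = 0.9 with metformin and 9.5 − 9.2 = 0.3 with placebo, so the difference in change is 0.6 (the final values differ by 0.5). The assumed effect is 1.5/0.6 = 2.5 times as large.

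**5. Power at 0.6 points, 29 per arm, two-sample t-test.** Only the SD of 2 comes from the protocol. The smaller values are assumptions, included because a baseline-adjusted or repeated-measures analysis may work with less residual variation.

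| SD | Power at 0.6 points |
|---|---|
| 2 (protocol) | 20% |
| 1.5 (assumed) | 32% |
| 1.25 (assumed) | 44% |
| 1.0 (assumed) | 61% |

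At SD 2, 80% power for 0.6 points would need 2 × 7.84 × (2/0.6)² = 174.2, so 175 per arm (normal approximation).

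**6. Can the repeated measurements make up the gap?** The design has 80% power for a standardised difference of 1.5/2 = 0.75. To reach the same power for 0.6 points, the effective SD would have to be 0.6/0.75 = 0.80. In variance terms that is 0.64 against 4, a reduction of 84%. The protocol states no correlation or residual SD that would support a reduction of that size.

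**The case against.** Several defences are sound.

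- **The numbers can be traced.** A reader might infer from the paired label that the sample size does not reproduce, or that the right answer is 14, since 7.84 × (2/1.5)² = 13.9. The documents do not support either reading. Both 29 and 74 follow from the stated inputs. The 14 requires treating SD 2 as the SD of within-pair differences, whereas the protocol gives it as the SD of HbA1c levels. With SD 2 for levels, a paired formula gives 28 at correlation 0 and 14 at correlation 0.5, and no correlation is stated.
- **The word conservative.** A reader might infer that the protocol calls the 1.5 points conservative. It does not. The word is tied to sizing on a simple comparison of means while a repeated-measures analysis is planned, and that argument has some merit.
- **Attrition.** The arithmetic does what the text says, which is to oversample by 25%, and the loss of power is under 2 percentage points.
- **Effect size.** The cited trials ran for 3 months against 9 here. The protocol notes that they did not specifically recruit double diabetes, and that metformin may work better in this group. A true effect above 0.6 is therefore possible.

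The first two points stand in full and limit the finding to the label and the missing context. The third stands as to size, but the claim of adequate numbers at the predicted attrition is still not met. The fourth is a fair caveat, but the protocol attaches no figure to it, and nothing it reports brings the expected difference near 1.5.

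**Conclusion.** The paragraph needs correcting, but the sample size itself is not miscalculated.

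- **Label:** wrong. The comparison is of two independent means, and 29 per arm is correct for it.
- **Attrition:** 74 covers 21.6%, not 25%. At 25% loss, power for 1.5 points is about 78% (t) or just under 80% (z). This is minor.
- **Effect size:** the material point. The 1.5 is unsourced and 2.5 times the difference in both cited trials. At 0.6 points with 29 per arm, power is about 20% at the protocol's SD and 32% to 61% across assumed SDs from 1.5 down to 1.0. Ignoring the repeated measurements is conservative in itself, but that gain would not plausibly offset the optimistic effect.

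The power figures assume a two-sample t-test on HbA1c and 29 completers per arm. A reader might go further and conclude that the trial is bound to be negative. That does not follow: the true effect in this population over 9 months is unknown, and at SD 1.0 the chance of detecting even 0.6 points is better than even.

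**What to change.** In item 4c:

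1. Replace the reference to paired means with a comparison of two independent means (two-sample t-test).
2. Keep 74, and state that it covers 21.6% attrition, or equivalently gives about 78% power for 1.5 points if 25% are lost. Bring *Subject Replacement* into line.
3. Restrict the word conservative to the repeated-measures argument, or delete it.
4. Say that the 1.5 points is an assumption, set it beside the 0.6 in the two cited trials with the caveats on duration and population, and give the power at 0.6 points: about 20% at SD 2, with the range for smaller SDs marked as assumed.

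The cost is a wording amendment and less favourable stated figures. No patients are added, and the design and analysis do not change.

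### The sample size is called conservative because repeated measurements must raise power, but the planned repeated-measures ANOVA does not guarantee that: the gain or loss depends on the tested term and the within-person correlation

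*Protocol*

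**What the plan says.** Protocol section 4c, under the sample size heading, says the calculations "are based on the simple comparison of paired means". It uses z = "1.96 for a two-tailed test" and "a statistical power of 80"%. The two assumptions are that "supplementing the treat-to-target protocol with metformin will decrease the Hb A1c level by at least 1.5 percent units" and that "the standard deviation for Hb A1c levels in obese adolescents is estimated to be 2". The result is 29 per arm, raised to 74 in total for attrition.

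The same paragraph ends by calling this conservative, since "the repeated measurements will, by construction, improve the power of the study", and presents that as protection if outcomes vary more than assumed.

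On timing: "All outcomes will be measured on an ongoing basis, at the beginning of the trial, and then at 3 months intervals". With nine months of treatment, the visits are months 0, 3, 6 and 9. The Visit III description has the month-0 blood drawn before the treat-to-target regimen and capsules start.

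On analysis, H1A states: "Consecutive HbA1c levels for patients with and without metformin will be compared using repeated-measures Analysis of variance (ANOVA). Analysis of covariance is added for gender and age. The text does not say whether the arm main effect or the arm-by-time term is the test, and it gives no correlation between a patient's visits.

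**The concern.** The sentence claims a power property without conditions. Repeated measurements can help, but a repeated-measures ANOVA offers more than one test, and the two obvious ones respond to correlation in opposite ways.

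- **Arm main effect.** It averages all visits in the model. At month 0 the randomised arms have an expected difference of zero, so including that visit shrinks the averaged effect. Averaging strongly correlated values removes little variance in return.
- **Arm-by-time.** It uses within-person change, so it is strong when visits are highly correlated and weak when they are not.

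Apart from the attrition allowance, this sentence is the only reserve the protocol claims. A reader relying on it would accept an SD above 2 as already covered.

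**Working it through.** **Inputs from the protocol:** two-sided 5%, difference 1.5, SD 2, 29 per arm, visits at months 0, 3, 6 and 9.

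**Assumptions not in the protocol:** all 29 per arm complete; equal correlation rho between any two visits (compound symmetry); the same SD at each visit; the full 1.5-point effect from month 3.

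**1. The protocol's own figure.** The two-sample normal formula gives n = 2 × (1.96 + 0.84)² × 2² / 1.5² = 27.9, so 28 per arm. The t-test version needs 29: noncentrality 1.5 / (2 × √(2/29)) = 2.86 on 56 df, power 80.1%. The stated 80% reproduces. (A genuinely paired formula would give about 14, so despite its label the figure is a two-sample one.)

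**2. Arm main effect over months 0 to 9.** This is a t-test on each patient's four-visit mean.
- Difference: (0 + 1.5 + 1.5 + 1.5) / 4 = 1.125
- SD of the mean: 2 × √((1 + 3rho)/4)

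| rho | SD of mean | noncentrality | power |
|---|---|---|---|
| 0.3 | 1.378 | 3.11 | 86% |
| 0.5 | 1.581 | 2.71 | 76% |
| 0.7 | 1.761 | 2.43 | 67% |
| 0.9 | 1.924 | 2.23 | 59% |

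It beats the single comparison only if (1 + 3rho)/4 < 0.75² = 0.5625, that is rho < 0.417.

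**3. Arm-by-time.** Noncentral F on 3 and 168 df. The squared deviations of the visit differences from their mean sum to 1.125² + 3 × 0.375² = 1.6875. The noncentrality is 29 × 1.6875 / (2 × 2² × (1 − rho)) = 6.117 / (1 − rho).

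| rho | noncentrality | power |
|---|---|---|
| 0.3 | 8.74 | 69% |
| 0.5 | 12.23 | 84% |
| 0.7 | 20.39 | 97.5% |

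It beats the single comparison only above rho of about 0.45.

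**4. Both together.** Below about 0.42 only the main effect gains; above about 0.45 only arm-by-time gains; in between neither does. At no rho do both terms improve on 80.1%. Simulation with 10,000 runs agrees: main effect 76.1% and arm-by-time 84.0% at rho 0.5; 66.0% and 97.5% at rho 0.7.

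**5. A further assumption, for sensitivity.** If the effect builds up as 0.5, 1.0 and 1.5 at months 3, 6 and 9, the main effect has 43%, 36% and 31% at rho 0.5, 0.7 and 0.9. Arm-by-time has 54% at rho 0.3 and 70% at rho 0.5.

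**6. Month-9 difference with month 0 as covariate.** The residual SD is 2 × √(1 − rho²).

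| rho | residual SD | noncentrality | power |
|---|---|---|---|
| 0.3 | 1.908 | 2.99 | 84% |
| 0.5 | 1.732 | 3.30 | 90% |
| 0.7 | 1.428 | 4.00 | 98% |

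At rho = 0 this falls back to the single comparison, about 80%.

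**The case against.** The strongest reply is that the protocol never names the arm main effect as its test and never says month 0 is averaged in as an outcome. H1A speaks of influence over time and H1B of a greater reduction, which fit arm-by-time at least as well. On that reading the protocol's optimism is largely right at moderate to high correlation: 84% at rho 0.5 and 97.5% at 0.7. The mean of months 3 to 9 alone also gains: 97%, 93%, 88% and 83% at rho 0.3, 0.5, 0.7 and 0.9. This stands.

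A reader might therefore wrongly infer from the main-effect figures that the trial has only 59% to 76% power. The documents do not support that. Those figures belong to one unnamed term over an assumed rho of 0.5 to 0.9, and the same term reaches 86% at rho 0.3. Nor can one say that the stated 80% is missed even when the protocol's assumptions are met: it was stated for the simple comparison, where it reproduces.

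Two further points have some force. The tested term and the handling of baseline are often left to the statistical analysis plan, so their absence is not the complaint; the complaint is the positive statement about power. And the sample size does not come from this sentence, so removing it changes no patient number.

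The attrition allowance does not rescue the claim. Even if all 37 per arm were retained, the main effect over months 0 to 9 would have 77% at rho 0.7 and 70% at rho 0.9.

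**Conclusion.** The statement that repeated measurements raise power by their nature is unsupported, and with it the unconditional description of the sample size as conservative. Relative to 80.1%, the planned ANOVA can gain or lose: 86% down to 59% for the arm main effect over months 0 to 9 as rho goes from 0.3 to 0.9, and 69% up to 97.5% for arm-by-time as rho goes from 0.3 to 0.7. These figures rest on 29 completers per arm, SD 2, compound symmetry and an immediate full effect. Rho and the time course are assumptions, not protocol figures. What fails is the guarantee, and so the reserve against larger variability. The 80% for the simple comparison is not in dispute here.

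**What to change.** In the sample size paragraph, remove the claim that power rises by construction and the unconditional word conservative. Name the deciding contrast: the between-arm HbA1c difference at month 9, from a model with months 3, 6 and 9 as outcomes and month 0 as a covariate rather than as an outcome visit. State the assumed correlation and the power for that contrast. Under the stated difference and SD, with 29 completers per arm, 80% is then a true lower bound, and it does not depend on how quickly the effect builds up before month 9.

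The cost is rewording one paragraph and a small change to the stated model, in the protocol or the statistical analysis plan. Month-0 HbA1c is already collected, so no patients, visits or samples are added.
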